People with PD have difficulties with the long-term consolidation of new motor skills [23], but adjunctive neuromodulatory techniques, such as non-invasive brain stimulation, may help to upregulate neuroplasticity and facilitate motor skill acquisition and retention [24]. Transcranial direct current stimulation (tDCS) is a therapeutic tool that has been used to attenuate motor symptoms of PD [24, 25] with few side effects (e.g., occasional headache/nausea and scalp itchiness) [24]. When applied to the primary motor cortex (M1), anodal tDCS (a-tDCS) can induce a lasting increase in M1 excitability and reduce cortical inhibition, resulting in improved functional performance [26]. When combined with other training modalities such as exercise or physical therapy, greater and longer-lasting improvements in motor function have been observed in healthy and clinical populations than with either treatment modality alone [27–29]. However, no studies have investigated the concurrent use of a-tDCS and exergaming in people with PD.

The aims of this study are to determine the effects of a 12-week concurrent exergaming and a-tDCS intervention on measures of static and dynamic balance and to evaluate any long-term residual effects. Additionally, we will employ transcranial magnetic stimulation (TMS) techniques in the M1 and functional near-infrared spectroscopy (fNIRS) in the left and right dorsolateral pre-frontal cortices (DLPFC) to determine neurophysiological mechanisms that may underpin changes in balance. We hypothesise that the combination of exergaming and a-tDCS will lead to greater and longer-lasting improvements in balance and neurophysiological measures than exergaming or usual care alone.

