## Methods/design

We will conduct a 24-week, exploratory, double-blind, randomised controlled trial to investigate the effects of a concurrent exergaming and a-tDCS intervention that includes a 12-week post-intervention follow-up period. Participants will be randomly allocated to one of three groups: (1) exergaming + a-tDCS, (2) exergaming + sham a-tDCS or (3) usual care (control). The trial will be conducted at the Institute for Physical Activity and Nutrition at Deakin University, Burwood, Melbourne, Australia. Ethical approval was granted by the Deakin University Human Research Ethics Committee (project number 2016-053), and the trial is registered with the Australian New Zealand Clinical Trials Registry (ACTRN12616000594426).

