### Sample size calculation

On the basis of data provided by Shih et al. [31], whose primary outcome was the LOS to assess reaction time and excursion endpoints in people with PD (Cohen’s *d* = 0.74, 77% improvement in reaction time, 89% improvement in endpoint excursion), a sample size calculation using G*Power statistical software estimated a sample size of five participants per group would be sufficient for 85% power (α = 0.05) while using a conservative estimated SD change of ± 5. It is difficult to determine if this is a large-enough sample size to detect change between the real and sham a-tDCS conditions, given the paucity of literature using a testing paradigm of exercise + real a-tDCS vs exercise + sham a-tDCS vs control. However, using the percentage changes between real and sham conditions reported by Kaski et al. [28], we postulate that a sample size of 18 participants will be enough to detect a medium effect size between the real and sham a-tDCS groups (Cohen’s *d* = 0.5) with an estimated SD change of ± 25 for the retropulsion pull test. The LOS and SOT measures were not used by Kaski et al. [28]; therefore, the retropulsion pull test was selected because it contains a balance perturbation similar to that of the SOT. Therefore, to accommodate for a 20% dropout rate, we aim to recruit 8 participants per group (24 participants in total).

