### Statistical analysis

Statistical analyses will be conducted using Stata version 11 statistical software (StataCorp, College Station, TX, USA). A generalised linear mixed model with factors for time (0, 6, 12 and 24 weeks), group (exergaming + sham a-tDCS vs exergaming + real a-tDCS vs control) and group-by-time interaction will be used to determine the effect that different direct current stimulation interventions have on brain excitability and balance. Potential factors such as the participant’s age and time since diagnosis will be used as covariates for analyses within our models. Per-protocol analysis will also be performed by including all participants who are at least 85% compliant with the exercise (as measured by the number of exercise sessions attended). Post hoc analyses using the Bonferroni correction will be applied as appropriate. Pearson’s product-moment correlation coefficient will be used to measure the level of correlation between change scores of the functional tests and brain excitability and activation. Significance will be set at *P* < 0.05.

When possible, we will try to obtain all endpoint measures from any dropouts in the final analysis. For participants who are lost to follow-up, missing data will be handled using the multiple imputation method [63]. Because the multiple imputation method assumes only that data are missing at random [64], we will additionally perform sensitivity analyses to evaluate the potential effect of non-random attrition [65]. Sensitivity analyses will involve testing a range of plausible scenarios in outcomes for participants who were lost during follow-up [66].

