## Discussion

Falls among people with PD incurs a considerable cost associated with hospitalisation and injury management or treatment. An economic report published in 2014 established that health system costs due to accidental falls represent an additional 22% of the total health cost of PD [67]. This translates to an additional estimated annual cost of $1487AUD per person with PD [67]. Exergaming is a mode of exercise that is engaging, adds diversity to a rehabilitation programme, can be performed at home and may be effective at improving functional capacity and reducing risk of falls in people with PD. However, by combining exergaming with a-tDCS (a primer for adaptive neuroplasticity), greater and longer-term improvements in motor function may be achieved. To date, there is limited evidence for the effectiveness of combined exergaming and a-tDCS to improve balance and lower limb function in people with PD. As such, we aim to use a double-blind, randomised controlled study protocol to explore the efficacy of concurrent a-tDCS and exergaming for improving static and dynamic balance over a period of 12 weeks. In addition, our secondary objectives of using TMS and fNIRS to measure neurophysiological changes in the M1 and DLPFC will potentially provide a mechanistic understanding of any functional changes observed. Last, few studies have addressed the consolidation of long-term motor skill retention following exercise and a-tDCS in people with PD, and therefore we aim to explore any residual improvements in balance, lower limb and/or neurophysiological function after a 12-week follow-up period.

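### The planned Pearson correlation of change scores has no term for arm; if it is pooled, parallel treatment effects alone can produce an apparent brain–balance link

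*Protocol article*

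**What the plan says.** The Statistical analysis section of the protocol article states that Pearson's coefficient will measure the "level of correlation between change scores of the functional tests and brain excitability and activation". It does not say whether the coefficient is computed over all participants, within each arm or after adjustment for arm.

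Group appears in the same section only as a factor in the mixed model. Age and time since diagnosis "will be used as covariates for analyses within our models", which does not reach the correlation. One threshold, P < 0.05, covers the whole section ("Significance will be set at").

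The correlation serves a stated aim. The Background says that TMS and fNIRS are used "to determine neurophysiological mechanisms that may underpin changes in balance", and the Discussion says that these measures "will potentially provide a mechanistic understanding of any functional changes observed".

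The abstract's discussion and the Background hypothesise that the combined arm will do better on both balance and neurophysiological measures. The Discussion expects a gradient in balance, with exergaming above control and real stimulation adding to it.

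**The concern.** In a randomised three-arm trial, arm is a common cause of both change scores. If treatment shifts the arm means of both in the same pattern, a coefficient computed over all participants picks up that shift. It then mixes two quantities: the difference between arms, and the association among people who received the same treatment. Only the second says whether participants whose brain measures changed more also gained more balance.

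The correlation is the only analysis described that links brain measures to function, since the mixed model takes each outcome separately. A pooled coefficient could restate the treatment effects and be read as evidence of mechanism. The pattern that causes this is the one the protocol hypothesises.

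**Working it through.** **Inputs.** Three arms (Methods/design). 8 per arm, 24 in total, after a 20% dropout allowance (Sample size calculation). Effect sizes d = 0.74 and d = 0.5 (same section). Two-sided α = 0.05; the sidedness is assumed. Arm separations on the brain measures are not given, so they are assumed and shown as a range.

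**The plan's own figure.** The article gives no figure for the correlation. Its recruitment target does reproduce: reading 18 as 6 per arm, 6/0.8 = 7.5, rounded up to 8 per arm, or 24.

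**Formula.** Let arm means be in within-arm SD units, with zero correlation within arms. Then

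pooled r = Cov_between(mx, my) / √[(1 + Var_between(mx)) (1 + Var_between(my))].

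- *Protocol effect sizes, added and applied to both measures (0, 0.74, 1.24):* the mean is 0.66 and the deviations are −0.66, 0.08 and 0.58. Variance = (0.4356 + 0.0064 + 0.3364)/3 = 0.2595. r = 0.2595/1.2595 = 0.21.
- *Both exergaming arms shifted equally (0, d, d):* variance = 2d²/9. At d = 1, r = 0.222/1.222 = 0.18. At d = 2, r = 0.889/1.889 = 0.47.
- *Unrelated patterns (0, d, 2d) and (0, d, 0):* the deviations are (−d, 0, d) and (−d/3, 2d/3, −d/3). Their products sum to d²/3 + 0 − d²/3 = 0, so r = 0 although the arms differ on both measures.

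**Rejection rates.** Simulated with 8 per arm, no within-arm correlation, independent unit-variance errors and at least 40,000 trials per scenario. The pooled test has 22 df and the arm-adjusted test 20 df. In the first four rows both measures follow the same pattern, one of (0, d/2, d), (0, d, d) or (0, 0, d).

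| Arm pattern | Mean pooled r | Pooled test significant |
|---|---|---|
| Matched, d = 0.5 | 0.04–0.06 | 5–6% |
| Matched, d = 0.74 | 0.09–0.11 | 7–8% |
| Matched, d = 1 | 0.15–0.19 | 10–14% |
| Matched, d = 2 | 0.41–0.48 | 54–73% |
| 0, 0.74, 1.24 on both | 0.21 | 16–17% |
| Partly aligned: function (0, d, d), brain (0, 0, d); d = 0.74 / 1 / 2 | 0.06 / 0.09 / 0.24 | 6% / 7% / 18% |
| Unrelated: (0, d, 2d) and (0, d, 0); d = 0.74 to 2 | 0.00 | 4.6% down to about 1.5% |

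The arm-adjusted correlation averages 0.00 and is significant in about 5% of trials in every row.

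**Opposite error.** With a true within-arm correlation of 0.5 and opposed arm means (0, 1, 2 and 0, −1, −2), the between-arm covariance is −2/3. Pooled r = (0.5 − 0.667)/1.667 = −0.10. The pooled test is significant in 6% of trials, the arm-adjusted test in 69%.

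**Cost of adjusting.** Critical |r| = t/√(df + t²). With 22 df, 2.074/√(22 + 4.301) = 0.404. With 20 df, 2.086/√(20 + 4.351) = 0.423.

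**The case against.** The strongest reply is that pooling is inferred. A Pearson coefficient within each arm would fit the sentence equally well, and the problem would then disappear. A condensed article may also leave this detail to an analysis plan that is not shown. This stands in part: the protocol cannot be said to have specified a pooled analysis. But it does name a method and a significance threshold, and it places group and covariates elsewhere. A reader who follows the text as written would compute one coefficient over everyone.

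A second reply is that the effect is modest at the protocol's own effect sizes and needs matched patterns to become large. This stands. A reader might infer that the analysis will show a mechanism whenever the arms differ on both measures. The documents and the arithmetic do not support that: the arm means must also move together, and even with matched patterns at 1 SD the pooled test is non-significant in 86–90% of trials. No section supports separations of 2 SD.

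Third, the trial is described as exploratory, the brain measures are secondary, the mechanistic claim is hedged, and the primary balance comparison includes group and is unaffected. All of this is true and limits the weight of the point.

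**Conclusion.** The point holds in a conditional form. If the correlation is pooled, as the wording suggests, it does not isolate the association among people within an arm. It can be inflated by parallel treatment effects or masked by opposed ones.

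The most protocol-based figure for the inflation is a false-positive rate of about 16–17%, roughly three times nominal. It assumes that d = 0.74 and 0.5 add and that both apply equally to the brain measure, which the protocol does not state. With a single matched separation of either size the rate is about 5–8%. The larger rates rest on assumed separations. All figures assume 8 per arm, normal errors and no within-arm correlation.

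The correction is worth making because it is nearly free and bears on a stated aim. It does not affect the primary analysis.

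**What to change.** State that the main correlation is the partial correlation of change scores adjusted for arm. Equivalently, correlate the residuals after subtracting each arm's mean, with 20 df at n = 24. Plot the points by arm. If a pooled, unadjusted coefficient is reported, label it descriptive and attach no mechanistic reading to it. If an analysis plan already specifies arm adjustment, one clarifying phrase in the protocol is enough.

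The cost is the two degrees of freedom shown above and one line of analysis code. No new data and no design change are needed.

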## Discussion

Falls among people with PD incurs a considerable cost associated with hospitalisation and injury management or treatment. An economic report published in 2014 established that health system costs due to accidental falls represent an additional 22% of the total health cost of PD [67]. This translates to an additional estimated annual cost of $1487AUD per person with PD [67]. Exergaming is a mode of exercise that is engaging, adds diversity to a rehabilitation programme, can be performed at home and may be effective at improving functional capacity and reducing risk of falls in people with PD. However, by combining exergaming with a-tDCS (a primer for adaptive neuroplasticity), greater and longer-term improvements in motor function may be achieved. To date, there is limited evidence for the effectiveness of combined exergaming and a-tDCS to improve balance and lower limb function in people with PD. As such, we aim to use a double-blind, randomised controlled study protocol to explore the efficacy of concurrent a-tDCS and exergaming for improving static and dynamic balance over a period of 12 weeks. In addition, our secondary objectives of using TMS and fNIRS to measure neurophysiological changes in the M1 and DLPFC will potentially provide a mechanistic understanding of any functional changes observed. Last, few studies have addressed the consolidation of long-term motor skill retention following exercise and a-tDCS in people with PD, and therefore we aim to explore any residual improvements in balance, lower limb and/or neurophysiological function after a 12-week follow-up period.

In our study, exergames are used to deliver cognitive and static and dynamic balance exercises for people with PD. The Jintronix software used in our study is capable of using an inexpensive, commercially available motion capture camera to deliver a vast selection of rehabilitation games from a personal computer or laptop. Additionally, the use of a-tDCS to augment adaptive neuroplasticity may lead to greater and longer-lasting improvements in balance and lower limb function in people with PD. Thus, we hypothesise that (1) balance will improve for the exergaming groups compared with controls and (2) the addition of real a-tDCS will provide additive improvements. Novel home care therapies that are easily administered are likely to maintain exercise enjoyment and facilitate long-term exercise adherence. Therefore, if this trial is successful, this intervention will potentially allow for a high degree of scalability into a community- or home-based setting, where exergames can be implemented either as part of a rehabilitation programme in health-care facilities (i.e., rehabilitation hospitals, age care facilities and nursing homes) or as an adjunctive therapy that can be performed at home in conjunction with standard therapy. Our study also has the potential to have wider implications for reducing total health-care costs (i.e., hospitalisation, injury management and assistive care costs) associated with falls for people with PD.

### Trial status

Eighteen participants have completed 24 weeks of training and are waiting to be tested at 3-month follow-up. No dropouts or adverse events have been reported.

## Abbreviations

1RM: One-repetition maximum
10MWT: 10-Metre Walk Test
4SST: Four Square Step Test
5TSTST: Five Times Sit to Stand Test
AE: Adverse event
a-tDCS: Anodal transcranial direct current stimulation
COP: Centre of pressure
CS: Conditioning stimulus
DLPFC: Dorsolateral pre-frontal cortex
fMRI: Functional magnetic resonance imaging
fNIRS: Functional near-infrared spectroscopy
HHb: Deoxygenated haemoglobin
ICC: Intraclass correlation coefficient
ISI: Interstimulus interval
LICI: Long-interval intracortical inhibition
LOS: Limits of Stability Test
M1: Primary motor cortex
mBest: Mini Balance Evaluation Systems Test
MCI: Mild cognitive impairment
MEP: Motor-evoked potential
O_2_Hb: Oxygenated haemoglobin
PD: Parkinson’s disease
QoL: Quality of life
RMT: Resting motor threshold
sEMG: Surface electromyography
SICI: Short-interval intracortical inhibition
SOT: Sensory Organization Test
SPIRIT: Standard Protocol Items: Recommendations for Interventional Trials
TA: Tibialis anterior
tDCS: Transcranial direct current stimulation
TMS: Transcranial magnetic stimulation
TS: Test stimulus
UPDRS: Unified Parkinson’s Disease Rating Scale
